
### Outline of the intervention

The intervention will last 6 months, since this is the minimum amount of time to achieve maintenance of changed behaviour. For the reasons described above, MI will be used as a counselling method. Based on the evidence for the effectiveness of frequent contacts, and on the preferences of the interviewed workers, 3 face-to-face and 4 telephone contacts will be scheduled. The first contact will always be face-to-face. The duration of a face-to-face contact will be 45–60 minutes. The telephone calls will take 15–30 minutes. Face-to-face contacts will preferably take place after participant's working hours (that is: after 3 pm) at the OHS. If a participant explicitly states that he does not want to visit the OHS, the counsellor may arrange a home visit. As suggested by the interviewed workers, the wife or partner of the participant will be invited to accompany the participant to the face-to-face meeting. Additionally, written materials will be provided. The intervention will be performed by 24 counsellors (occupational nurses and OPs) who have been trained for the purpose of this study. Each participant will be in contact with one specific counsellor during the entire intervention. Each participant in the intervention group will be allocated to a counsellor in his own region of residence. The counsellor will strive to arrange the first contact within the first week after inclusion, and arrange further contacts each month, with a margin of one week. The last telephone contact should take place in the 25^th ^week after inclusion at the latest. The schedule for each participant in the intervention group is presented in Table 2.

**Table 2 T2:** Contacts schedule for each participant in the intervention group.

**T in weeks**	**Event**
0	Invitation for first face-to-face encounter.
1	Face-to-face contact
4	Telephone contact
8	Face-to-face contact
12	Telephone contact
16	Telephone contact
20	Face-to-face contact
23	Telephone contact
26	First follow-up measurement
52	Second follow-up measurement.

### Training of counsellors and pilot study

All counsellors were trained in MI by an MI- expert. Before the training took place, they were asked to read a short introduction to MI and background information about healthy lifestyle [40], which was sent to them by the principal investigator. In a 3-day course they learned the principles of MI and practiced by means of role-plays, after which they gave feedback to each other. In a pilot study among a small group of construction workers (n = 19), half of the counsellors had a meeting with one or two workers. These counsellors recorded their conversation(s) in the pilot study on audiotape. The tapes were evaluated on the 3^rd ^training session, which was held 6 weeks after the first two-day training session. In this 3^rd ^session, difficulties experienced during the pilot were discussed. Further aims of the pilot study were to assess both the counsellors' and the workers' opinions about the face-to-face contacts, and to test the questionnaire and 8 different brochures about CVD and lifestyle. After the pilot study, comments and suggestions for improvement of the intervention were assessed by the principal investigator by means of evaluation forms. Besides, 7 randomly chosen participants were personally interviewed about their experiences in the pilot. All workers and counsellors were positive about the face-to-face contacts. After the pilot, no major changes needed to be made in the study protocol. As suggested by the participants of the pilot study, the number of brochures to be provided was reduced.

### Counselling protocol

Using MI, the counsellor will guide the participant through the process of becoming aware of the health problem, changing behaviour and maintaining the changed behaviour, as described in the literature. The following steps will be undertaken to reach these goals.

#### Step 1: Introduction of health problem

In the first face-to-face encounter, the counsellor will explain the goals and procedure of the intervention. He or she will discuss the participants' knowledge about CVD risk factors and health consequences, as well as his awareness of his own risk. A personal risk profile, on which the participant's values on five important risk factors (BMI, systolic blood pressure, total cholesterol, days per week involved in PA of moderate intensity, smoking) are visually represented, will be given to the participant and will be explained in a clear way. The counsellor will not move on to the next subject until the worker understands this information. Current lifestyle and family history will be discussed, to get a complete insight in the participants' lifestyle and health status.

#### Step 2: Choosing type of intervention

Two types of intervention will be offered: 1) an energy balance intervention and 2) a smoking cessation intervention. Together with the counsellor, the smoker will choose one of the two intervention types, based on his personal risk profile and his own preferences. He will be encouraged to make his choice during the first meeting, and to stick to his first choice. However, if later on during the intervention, the participant desires to switch intervention types or if he prefers to address both smoking and energy balance, this will be possible. In case a participant is not ready make his choice in the first meeting yet, e.g. because he is confused by his risk profile, he will be allowed to make his choice during the 2^nd ^contact. In the energy balance intervention, both diet and PA will be addressed. Depending on the current PA and dietary behaviour of the participant, the focus will be on diet or daily PA. In improving dietary and PA behaviour, sub-behaviours will be chosen to address, which will be relevant to the participant and feasible, e.g. reducing fat intake or cycling in leisure time.

#### Step 3: Exploring ambivalence

By discussing advantages and disadvantages of a current sub-behaviour (e.g. eating too many snacks, not participating in any sports) as well as of the 'desired' healthy behaviour, ambivalence may be raised. On a 'decisional balance quadrant', the worker will fill in the 'pros of his current behaviour', 'cons of his current behaviour', 'pros of behaviour change' and 'cons of behaviour change'. In doing so, he may become aware of the discrepancy between his current behaviour and the desired behaviour, possibly leading to a change in attitude towards the desired behaviour. As a result, he may realise that it is worth the effort to change his current behaviour.

#### Step 4: Determining readiness, willingness and ability

In step 4, the participant will be asked to indicate his perceived *importance *of change, his perceived *confidence *in his ability to change, and his *readiness *to change on a scale from 0 (not at all) to 10 (highly) [41]. The counsellor will ask why he did not choose a lower number, and what should be done to get him higher up the scale. In doing so, the counsellor and participant may find out which of these items is the most important barrier for change, so that special attention can be paid to that particular item.

#### Step 5: Goal setting

Social influence, the workers' environment and other factors that may influence behaviour will be discussed to facilitate goal setting. At the end of each meeting, a specific short-term goal will be defined by each participant and his counsellor, e.g. visiting the sports centre, reducing the number of snacks per week, or informing family and friends about the intended lifestyle change. This goal will need to be accomplished before the next meeting. In addition, after the first meeting one or more long-term goal(s) will be defined, for example loosing 20 pounds or quitting smoking. These goals need to be accomplished within six months.

Steps 1, 2, 3 and 4 will be discussed preferably in the first session. In the subsequent contacts, progress and obstacles for change will be discussed. Depending on the participants' situation, attitude, social influence, self-efficacy, environmental factors, habits or other determinants may be discussed, to facilitate the process of behaviour change. A new short-term goal will be set after each contact. If the participant asks for information about healthier lifestyle or suggestions for implementation, e.g. where to find a good fitness centre or how to prepare a low-calorie meal, the counsellor will provide this information. A small number of participants may not be of Dutch origin. Their lifestyle and especially dietary habits may be different from the Dutch white Europeans [42]. This will be taken into account by the counsellor when giving advice. The counsellor will stress the importance of incorporating the healthy behaviour into daily life, since this is the best way to achieve maintenance. In case a participant relapses into previous behaviour, the counsellor will guide him through the stages again, taking into account the problems of the past experience [5,31,33].

### Registration forms

During the first contact the counsellor and participant will complete a sheet that contains a summary of what has been discussed in steps 1 and 2, the decisional balance quadrant, the 10-point scales about importance, confidence and readiness, the first short-term goals and the long-term goal(s) (step 3, 4 and 5, respectively). The participant will take this sheet home as a reminder of what was discussed. Further, after each contact, the counsellor will fill in the location and duration of the contact, a summary of the topics discussed, and the (new) short-term goal on a short form. All sheets and forms will be sent to the research assistant, who is then able to check if and how the contacts are taking place.

### Written information

The counsellor will provide several brochures to each participant. The brochure 'Cardiovascular diseases' contains general information on lifestyle-related ailments of the heart, the brain and the vessels. The participants in the 'smoking cessation' intervention will receive a brochure from Stivoro, a Dutch organisation for education about the risks of smoking, describing benefits of smoking cessation, how to prepare a quit attempt, how to prevent relapse, et cetera. Participants in the 'energy balance' intervention will receive a brochure about PA, including guidelines and a training schedule. Furthermore, they will receive four brochures about healthy diet from the Dutch Heart Foundation and the Dutch Nutrition Centre: 1) A brochure with the dietary guidelines of the Dutch Nutrition Centre promoting a varied diet, low in saturated fat and rich in fruits, vegetables and bread, 2) A leaflet describing products high in saturated fat and their low-fat alternatives, 3) A leaflet with the caloric values of the most common food products, 4) A brochure with recipes for healthy meals.

### Incentives

Incentives will be handed out to all participants in the intervention group as well as those in the control group, to make participation more attractive and to avoid loss to follow-up. After 3 months, a t-shirt with the study logo will be sent. Along with the invitations for both follow-up measurements, a lottery ticket will be sent. Among the participants who attend the 2^nd ^follow-up measurement (T = 52 weeks), a heart rate measurement instrument will be raffled. At the same time, a 3-day stay in a bungalow park can be won by the participant who best completes a slogan. At the end of the second follow-up measurement, a step counter will be handed out to all participants.

### Quality assessment

To assess the quality of MI during the intervention, the Motivational Interviewing Treatment Integrity code (MITI) protocol will be applied to two face-to-face contacts of half of the counsellors during the first three months of the intervention. For this purpose, each counsellor will be asked to tape record 2 face-to-face contacts. The principal investigator will randomly choose a 10-minute lasting fragment from each tape, and make a transcript of the verbal communication on paper. Two independent MI-experts will code these fragments by using the MITI protocol [43]. The coding provides two scores: a 'global score' and a 'behaviour count'. The global scores refer to the entire verbal interaction between the participant and the counsellor. A global score for MI spirit as well as for MI empathy will be assigned as a single number on a 7-point scale. The behaviour count is a one-figure rating applied to the separate MI techniques, e.g. reflective listening and asking open questions. Any utterance may be assigned one of 6 primary behaviour codes. After coding, the counsellor will get feedback on his/her performance of MI.

### Measurements

Baseline data will be obtained from the PHS and the additional questionnaire. Six months after inclusion, a follow-up measurement will take place. Twelve months after inclusion, the second follow-up measurement will take place.

### Primary outcome measures

#### Physical activity

The main outcome measure for PA is whether the participant has started to fulfil one or both of the Public Health recommendations for PA. If so, he is considered to have changed from physically inactive to physically active.

On the PHS questionnaire, he will fill in how many days per week he usually is moderately physically active for more than 30 minutes. From this item, fulfilling the Public Health recommendation for moderate PA can be determined. Furthermore, he will be asked how many days during the last month he has performed vigorous physical activities that lasted long enough to make him sweat. By this item, fulfilling the Public Health recommendation for vigorous PA can be computed. Another outcome measure for PA is the frequency, duration and intensity of PA in leisure time. This will be assessed using the Short QUestionnaire to ASsess Health enhancing physical activity (SQUASH), which was shown to be a fairly reliable and valid questionnaire (*r*_*Spearman *_0.58 and *r*_*Spearman *_0.45 respectively) [44]. The SQUASH was designed to measure four clusters of PA, i.e. commuting activities, household activities, activities at work and school, and leisure time activities. For the purpose of this study, only commuting activities and leisure time activities, i.e. walking, cycling, gardening, odd jobs and sports will be measured, as these activities are considered relevant for the target group. The participant will be asked to fill in how many days per week and how many minutes per day he usually spends on these physical activities, during a usual week within the past month. The level of exertion for each type of activity will have to be indicated as well. The level of exertion for sports, gardening and odd jobs is classified as light, intermediate, and vigorous. The level of exertion for walking and cycling is classified as slow, intermediate, and fast. From the SQUASH, metabolic equivalents (METs) can be estimated. Light activities are rated as 2.0 to < 4.0 METs, moderate activities are rated as ≥ 4.0 to <6.5 METs, vigorous activities are rated as ≥ 6.5 METs [44]. The cluster items about household activities will be left out of the SQUASH questionnaire, as we expect these activities not to be major contributors to daily PA in this population of male construction workers. In addition, the SQUASH items about activities at work and school were not considered suitable for our population. The level of exertion, i.e. light, intermediate, or vigorous, of the daily activities at work will be assessed using a single question derived from the TNO questionnaire PA at work [45], which has not been tested for validity and reliability yet.

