## Background

In the Netherlands, cardiovascular diseases (CVD) are responsible for one third of all deaths each year. Besides to premature death and a decreased quality of life, CVD morbidity leads to high costs for health care and loss of productivity [1]. An unhealthy lifestyle, e.g. smoking, unhealthy diet and/or insufficient daily physical activity PA, is a major cause of CVD [2]. Well-known consequences of an unhealthy lifestyle are overweight, an unfavourable total/HDL cholesterol ratio, and an elevated blood pressure [3,4]. Improved lifestyle may contribute to an improved CVD risk profile. As to smoking cessation, it has been shown that those who have quit smoking quickly reduced the risk of CVD [2,5]. As to diet, there are several ways to decrease the CVD risk. For instance, diminishing intake of saturated fat will lower LDL and total cholesterol [2]. A diet low in salt has a beneficial effect on blood pressure [6]. Fruits and vegetables are rich in micronutrients and fibre and therefore protective against CVD [7]. Moreover, obesity, a major CVD risk factor, may be prevented by lowering calorie intake [8]. As to PA, there is sufficient evidence that regular PA is beneficial for health, not only by preventing weight gain but also by improving cardio respiratory fitness (CRF) [9,10]. In 1995, the Centers for Disease Control and Prevention (CDC) and the American College of Sports Medicine (ACSM) achieved consensus about the level of PA needed for good health. This recommendation stated that every adult should accumulate 30 minutes or more of moderate-intensity PA on most, preferably all, days of the week [11]. Next to this Public Health recommendation on moderate PA, the ACSM stated that each adult should perform vigorous exercise for 20 minutes or more, at least 3 times a week in order to improve CRF [12]. Like in the general Dutch population, an unhealthy lifestyle is commonly seen in Dutch construction industry. Even though the percentage of construction workers that fulfilled the guideline for moderate PA in 2005 (61%) was higher than that of the general Dutch male population (51%) [13], the prevalence of overweight and obesity in the construction industry was considerably higher than in the general Dutch population (64% vs. 51% and 15% vs. 10%, respectively). Only 18% of construction workers fulfilled the guideline for vigorous PA, as compared to 25% of the general Dutch male population. Furthermore, one third of all workers in the construction industry are smokers [14]. Since a substantial part of the ageing population in construction industry has an unhealthy lifestyle, CVD morbidity and mortality in this population is likely to rise in the following years. Sickness absenteeism due to CVD and other chronic diseases may also increase. In collaboration with Arbouw, a national organisation involved in monitoring and improving working conditions and occupational health of workers in construction industry, we will investigate the effectiveness and cost-effectiveness of an individual lifestyle intervention for male construction workers at risk for CVD. The aim of the intervention is to lower the risk for CVD by changing one or more lifestyle behaviours. As the intervention will be focussed on improving three lifestyle topics, i.e. diet, PA, and smoking, we hypothesise that in the intervention group diet will be improved, the amount of PA will be increased, and the number of smokers will be lowered. As these lifestyle components are important CVD risk factors, we further hypothesise that mean BMI, blood pressure, HbA1c and total cholesterol will be lowered and HDL cholesterol will be increased as a result of the intervention. In this article we will describe the design of this study, which has been named 'Health under Construction'.

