### Sample size calculation

The sample size is based on detecting a difference in daily PA according to the guideline for moderate intensity PA. Previous PHSs (2005) showed that 38% of construction workers with an elevated CVD risk was physically inactive according to this guideline. To show a 10% difference between the intervention and the control group after 26 weeks, i.e. 38% inactivity in the control group and 28% inactivity in the intervention group, with a power of 80% and a 95% confidence interval (α = 0.05), 692 persons will be needed (346 in each group). As we expect a loss to follow-up of 20%, 866 persons will be included at baseline. Based on an assumed initial non-response of 50%, we will invite 1,732 workers. In The Netherlands, each month approximately 3,334 workers are screened in a PHS. Based on PHS data obtained in 2006, we expect that on average approximately 667 of them (20%) will fulfil the inclusion criteria. Therefore, we expect that the recruitment period will last at least 3 months. The numbers are presented in Figure 1.

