### Data analysis

On all outcome measures, intention-to-treat analyses will be performed. Both crude and adjusted linear and logistic regression analyses will be performed. In doing so, analysis for covariance will be conducted adjusting for the outcome variable measured at baseline. In the adjusted model, other potential confounders will be included as covariate, such as age and work activities. Furthermore, effect modification, e.g. by family history, will be checked. First of all, data will be analysed for the whole intervention group, that is, irrespective of the intervention received. Secondly, subgroup analysis will be done among those having received the smoking or the energy balance intervention. As all participants will have to indicate at baseline which lifestyle behaviour they prefer to change, the participants in each intervention subgroup will be compared to those in the control group having indicated the same type of intervention preference. Cost-effectiveness ratios will be calculated by dividing the difference between the mean total costs between the two study groups by the difference in the mean effects. For each outcome measure used in this evaluation, cost-effectiveness ratios will be presented graphically on a cost-effectiveness plane. To calculate the confidence intervals for the ratios, bootstrapping will be done. For all analyses, a significance of 0.05 will be applied. On the process evaluation, qualitative analyses will be performed.

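### The declared main physical activity outcome (starting either guideline) is not the outcome that was powered (inactivity on the moderate guideline) and does not fit the baseline-adjusted analysis, so the stated 80% power does not describe it

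*Protocol article*

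**What the plan says.** Four parts of the protocol article bear on this.

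- **Sample size calculation.** "The sample size is based on detecting a difference in daily PA according to the guideline for moderate intensity PA". The planning rate comes from 2005 screening data, in which "38% of construction workers with an elevated CVD risk was physically inactive according to this guideline". The target is "38% inactivity in the control group and 28% inactivity in the intervention group", and the time point is fixed as well: "To show a 10% difference between the intervention and the control group after 26 weeks". This gives 346 men per group.
- **Primary outcome measures, Physical activity.** The declared outcome is worded differently: "The main outcome measure for PA is whether the participant has started to fulfil one or both of the Public Health recommendations for PA". The next sentence explains this as a change from physically inactive to physically active.
- **Table 1 (inclusion criteria).** Fulfilling neither guideline is one of six alternative risk factors, and any one of them is enough. Men who are already active can therefore enter the trial.
- **Data analysis.** All outcomes are analysed by intention to treat with linear or logistic regression, and "analysis for covariance will be conducted adjusting for the outcome variable measured at baseline".

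**The concern.** The powered outcome and the declared outcome differ in three ways: the guideline (moderate only, or either one), the type of variable (status at 26 weeks, or a one-way change), and who can have the event (every man, or only men inactive at baseline).

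Three consequences follow:

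- The article does not say whether men active at baseline are left out or counted as non-starters.
- A start-only outcome does not register men who lapse, whereas 38% and 28% are net prevalences that do. An arm could show more starters and no net gain in activity.
- A start has no value at baseline, so the adjustment in Data analysis has nothing to act on.

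Physical activity is the only primary outcome with a sample size. If its guideline, denominator and treatment of lapses stay open, they could be settled after the data are seen, and the answers could differ.

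**Working it through.** **Inputs from the document.** 38% and 28% inactive, α = 0.05, 80% power and 346 per group (Sample size calculation); 18% of all construction workers meeting the vigorous guideline (Background). Two-sided testing is not stated, but it is the reading that reproduces the figure.

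**Step 1: the plan's own figure.** Pooled two-proportion formula, with p̄ = (0.38 + 0.28)/2 = 0.33:

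n = [1.96·√(2·0.33·0.67) + 0.8416·√(0.38·0.62 + 0.28·0.72)]² / 0.10² = (1.3033 + 0.5565)² / 0.01 = 345.9, so 346 per arm and 692 in total. Power at 346 per arm is 80.0%. The arithmetic is sound for the outcome it describes.

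**Step 2: men who can start.** If 38% of the analysed men are inactive on the moderate guideline at baseline, 0.38 × 346 ≈ 131 per arm can start it. The other 215 or so cannot.

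**Step 3: power for starting, same N.** The document gives no start rate and does not divide the effect between more starts and fewer lapses, so both are assumed. If a fraction f of the 10-point net difference comes from starters, the difference in start rate among inactive men is 0.10·f/0.38. That is 13.2 points for f = 0.5, 17.1 for f = 0.65 and 26.3 for f = 1. The formula of step 1, solved for power, gives:

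| Control start rate | f = 0.5, 131 inactive men per arm | f = 0.65, 131 per arm | f = 1, 131 per arm | f = 0.5, all 346 per arm | f = 1, all 346 per arm |
|---|---|---|---|---|---|
| 10% | 82% | 95% | 99.9% | 77% | 99.7% |
| 20% | 68% | 87% | 99.6% | 59% | 98% |
| 30% | 60% | 82% | 99.2% | 48% | 95% |
| 40% | 57% | 79% | 99.2% | 41% | 91% |
| 50% | 57% | 81% | 99.5% | 36% | 87% |

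The last two columns count men active at baseline as non-starters. Power falls on either side of 80%, depending on quantities that the document does not give.

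**Step 4: the either-guideline definition as a follow-up status.** Its control rate is not given. If the 18% applied to this population, inactivity on both guidelines would be 0.38 × 0.82 = 31% under independence, and at least 0.38 − 0.18 = 20%. With 346 per arm and the same relative reduction (28/38), power is 68%, 56% and 45% at control rates of 31%, 25% and 20%. With a fixed 10-point difference it is 85%, 91% and 96%. Here too the stated 80% does not carry over.

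**Step 5: the regression model.** Suppose baseline activity is the covariate and active men are coded as non-starters. No active man can then have the event, and the covariate predicts non-event perfectly (quasi-complete separation). If only inactive men are analysed, the covariate is constant. The adjustment works as written only if the outcome is status at follow-up, which the Physical activity section does not say.

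**The case against.** The strongest reply is that Data analysis already implies the right method. Logistic regression of guideline fulfilment by intention to treat, adjusted for its baseline value, is follow-up status adjusted for baseline status, and the word started may only describe the change that such a model estimates. No sentence excludes active men or says that lapses are ignored, and a full protocol may hold the coding rules. This reading is possible, but the article does not state it. The outcome definition explicitly describes a change from inactive to active, and even the generous reading leaves moderate-only in one section against either guideline in the other.

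The reply is right to resist several stronger readings:

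- **The trial is underpowered.** A reader might infer this by applying 10 points to the 131 inactive men: power is 62%, 46%, 40% and 37% at control start rates of 10%, 20%, 30% and 40%. But 10 points among 38% of the men is only 3.8 points overall. For that effect (38% against 34.2%, 346 per arm) the powered outcome itself has about 18% power. The low figures reflect a smaller effect, not a loss caused by the definition.
- **Power is near-certain only if starters supply the whole effect.** This is not so. At a 10% control start rate, 85% of the effect coming from starters already gives 99.5%.
- **No more than 38% of enrolled men can be inactive.** The 38% is a planning figure from 2005, and inactivity is itself a route into the trial, so it is not a ceiling.
- **The vigorous guideline cannot be derived.** The Background requires that "each adult should perform vigorous exercise for 20 minutes or more, at least 3 times a week", while the questionnaire asks "how many days during the last month he has performed vigorous physical activities that lasted long enough to make him sweat". Sweating is a rough proxy for duration, so this is a side issue. Replacing the item with the SQUASH would omit activity at work.

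The moderate guideline is also not the only defensible choice: the either-guideline definition matches Table 1.

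**Conclusion.** The point holds as a mismatch between the powered, the declared and the analysed outcome. The sample size calculation is correct for moderate-guideline inactivity at 26 weeks in all men. Its 80% is not a statement about starting either guideline, and a start variable does not fit the planned baseline adjustment.

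The direction of the difference in power cannot be fixed from the document. With 131 inactive men per arm and control start rates of 10% to 50%, power is about 57% to 82% if half of the net effect comes from starters and above 99% if all of it does. These ranges assume 346 analysed men per arm, 38% inactive at baseline, the moderate guideline as the one being started, and start rates that the document does not supply.

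**What to change.** Define the main physical activity outcome as fulfils or does not fulfil the moderate guideline at 26 weeks, in all randomised men. Analyse it by logistic regression adjusted for the same status at baseline. The powered, declared and analysed outcomes are then the same, and the existing sample size applies. Report fulfilment of either guideline as secondary, using the screening questionnaire items as planned, and report starts and lapses by arm descriptively.

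If the sponsor prefers the either-guideline definition, it should still be analysed as follow-up status adjusted for baseline, with planning rates and power restated for it.

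The cost is wording in the Physical activity and Data analysis sections; no new data are needed. The preference for the either-guideline definition would add a revised power statement. The small downside is that the headline result moves from starters to net prevalence.
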